## Introduction

1

The most common sleep disorder in the world, insomnia is defined by clinically frequent and persistent problems getting to sleep, staying asleep, and/or waking up early. It is also characterized by dysfunction during the day, including weariness or low energy, mood swings, and cognitive decline (1). According to reports, 10% of people fit the diagnostic criteria for insomnia, while an additional 15%–20% of adults sporadically experience the symptoms of insomnia, with the percentage of adults experiencing insomnia rising each (2, 3). Patients’ physical and mental well-being are gravely endangered by insomnia, which also places a significant financial strain on the healthcare system (4). Research has demonstrated that sleeplessness raises the risk of a number of chronic physical illnesses, including diabetes, hypertension, heart disease, cancers, and mental health issues (5–8). The neurobiological mechanisms of insomnia are unknown, and most scholars believe that insomnia occurs as a result of psychological and physiological hyperarousal of the organism. Current diagnostic methods for insomnia rely on subjective patient reports, sleep diaries, and clinical interviews, and lack quick and accurate objective markers, such that insomnia is underdiagnosed in primary care settings thus leading to exacerbation of the condition (9–11). In addition, insomniacs undergoing treatment may lack objective knowledge and suffer from deep cognitive rumination, thus compromising clinical outcomes. Modern medical treatment of insomnia includes medication and cognitive behavioral therapy. However, commonly used sedative and sleeping medications in clinical practice are often accompanied by different degrees of adverse effects, including dizziness, headache, daytime sleepiness, and increased risk of dementia, leading to low patient acceptance (12). Cognitive-behavioral therapy is a first-line therapy recommended by clinical guidelines, which is more difficult to implement clinically due to its lack of professional resources, time-consuming nature, and poor patient compliance (13). Electroacupuncture is effective in treating insomnia with a non-placebo effect (14), but the specific mechanism of its effect is unknown, and its efficacy assessment is mainly based on the patient’s subjective scale, which lacks objective assessment indexes and testing methods.

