##### Inclusion criteria for insomnia patients

2.2.2.1

Age 18-60 years old;Meet ICSD-3 diagnostic criteria;5 points < PSQI < 17 points;not receiving psychotropic medication;have no communication or cognitive impairment and can perform basic operations on a smartphone;Signed informed consent.

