##### Inclusion criteria for healthy people

2.2.2.2

Normal blood count, liver function, kidney function, electrocardiogram, blood glucose, and blood lipid after consultation and health examination; healthy, no previous organic or functional diseases or psychiatric disorders;Be in the age range of 18 to 60;not recently participated in other clinical studies;Voluntarily participate in this trial, agree to and sign the informed consent form.

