##### Exclusion criteria for healthy people

2.2.3.2

Pregnant and lactating women;Alcoholics and smokers.

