##### PSQI

2.8.1.1

A questionnaire was used to evaluate the quality of sleep in a population, including 7 components: sleep quality, time to sleep, sleep duration, sleep efficiency, sleep disorders, hypnotic medications, and daytime dysfunction. The total score of the PSQI is 0-21, and the level of the score is inversely related to the quality of sleep, i.e., the higher PSQI score suggests a worse quality of sleep. A score of ≥5 on the PSQI indicates that clinical treatment may be needed, and the present study used a PSQI score of 5 < PSQI < 17 points as the inclusion criteria for insomnia.

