#### Assessment time point

2.8.3

The insomnia group will have the above information completed at enrollment and after 12 treatments, the scale will be collected again at 3 months follow up, and the health group will have serum collected only at the first enrollment.

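### The healthy-group criteria name no sleep measure, so controls with unrecognised insomnia can enter and modestly dilute the contrast that defines the insomnia metabolites

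*Protocol article*

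**What the plan says.** All references are to the Protocol article.

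**Patients.** Section 2.2.2.1 selects on sleep explicitly: "Meet ICSD-3 diagnostic criteria;5 points < PSQI < 17 points". Section 2.2.3.1 also excludes other sleep disorders: obstructive sleep apnea, REM sleep disorder and restless legs syndrome.

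**Healthy people.** Section 2.2.2.2 asks for "Normal blood count, liver function, kidney function, electrocardiogram, blood glucose, and blood lipid after consultation and health examination" and then "healthy, no previous organic or functional diseases or psychiatric disorders". Age limits, no recent participation in another trial, and consent make up the rest. The exclusions in 2.2.3.2 are only "Pregnant and lactating women;Alcoholics and smokers". None of these items mentions sleep.

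**Assessments.** Section 2.8.3 says that "the health group will have serum collected only at the first enrollment". The abstract and 2.1 likewise mention only serum for this group and place the scales with the insomnia group.

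**Role of the group.** Section 2.1 compares Group A with the healthy group in the untargeted screen and sends the differential metabolites found there to targeted quantification in Group B. The Discussion describes the same sequence, followed by a look at whether the abnormalities move back after treatment.

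**Background on insomnia.** The Introduction states that "10% of people fit the diagnostic criteria for insomnia" and that "insomnia is underdiagnosed in primary care settings". It adds that a further 15%–20% of adults have symptoms now and then.

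**The concern.** The factor that separates the two sides of the discovery contrast is measured on one side only. A history clause works through recognition: someone who has never been diagnosed, or does not regard poor sleep as a disease, can truthfully report no previous illness. Blood tests and an ECG do not detect insomnia. The article's own remark on underdiagnosis makes this a realistic route of entry.

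Each such person makes the control group more like the patient group. The expected difference shrinks, true markers become easier to miss, and a missed marker never reaches the targeted stage. The healthy level that gives the direction of an insomnia abnormality also moves toward the patients. If no sleep measure is taken at the healthy visit, the extent of the problem can be neither estimated nor corrected afterwards.

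**Working it through.** **1. The article's own sample size (2.3).** Inputs: mean change 2.63, SD 3.32, alpha 0.05, power 0.9, allocation 2:1. The sidedness of alpha is not stated; two-sided is assumed.
- d = 2.63 / 3.32 = 0.79, which the article rounds to 0.8.
- Controls = (1.960 + 1.282)² × (1 + 1/2) / 0.79² ≈ 25.1, so 26, with 52 patients. The stated 52 and 26 are reproduced. A one-sided test gives 21 and 42 and does not fit.

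**2. Inputs for the dilution check.**
- Group sizes: 33 healthy and 33 in Group A (66 patients split 1:1).
- d = 0.8. This is borrowed from the PSQI calculation, because the article gives no effect size for any metabolite.
- c = share of controls with unrecognised insomnia. The upper bound is 10%, the Introduction's population rate with nobody removed by the health check. As an illustration, 5% assumes that half are removed.
- Affected controls are assumed to carry the full patient shift. Each metabolite is tested at two-sided 0.05 with no multiplicity correction.

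**3. Expected numbers at the upper bound.**
- 33 × 0.10 = 3.3 controls.
- Chance of at least one: 1 − 0.9³³ = 0.969, about 97%.

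**4. Effect on the contrast.** With c contaminated, the mean difference is d(1 − c). Two versions were run:
- simple: SD left at 1;
- mixture: control variance raised to 1 + c(1 − c)d², averaged with the patient variance of 1.

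At c = 10%, the simple version gives 0.8 × 0.9 = 0.72. In the mixture version the control variance is 1 + 0.10 × 0.90 × 0.64 = 1.058, the pooled SD is √((1 + 1.058)/2) = 1.014, and d is 0.72 / 1.014 = 0.71.

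| c | d (simple / mixture) | Power, normal approximation (simple) | Power, t-test (simple) | Power, t-test (mixture) |
|---|---|---|---|---|
| 0 | 0.80 / 0.80 | 90% | 89% | 89% |
| 5% | 0.76 / 0.75 | 87% | 86% | 85.5% |
| 10% | 0.72 / 0.71 | 83% | 82% | 81% |

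At the upper bound the loss is about 7 to 8 percentage points. At 5% it is 3 to 4.

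**5. A scenario not relied on.** Adding the 15%–20% with occasional symptoms gives c = 25–30%, or 8 to 10 of 33 controls, and t-test power of 65–58% in the mixture version. This gives the full insomnia signature to people whom the Introduction sets apart from those meeting diagnostic criteria. It shows the direction only.

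**The case against.** The strongest reply is that controls are not unscreened. They have a consultation and a health examination, and the history clause is broad: on its face it covers known insomnia, sleep apnea, REM sleep disorder and restless legs. Insomnia, as the Introduction describes it, is persistent and impairs the day, so a careful consultation might bring it out. This stands. A reader might infer that sleep disorders are simply permitted among controls; the text does not support that. The gap is limited to what has not been recognised.

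Second, the sentence in 2.8.3 can be read as limiting when serum is taken rather than as ruling out a questionnaire, and the schedule (Figure 2) is not shown. This stands as a caveat: if the schedule or full protocol gives controls a PSQI, sleep status can be checked after all. The eligibility lists would still contain no sleep criterion.

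Third, the figures are pessimistic. Disease-free, non-smoking volunteers need not carry the population rate, and 0.8 is not a metabolite effect. This also stands, which is why 10% is treated as a bound. A reader might infer that contaminated controls would hide the insomnia metabolites altogether. At 5–10% contamination the calculation shows a modest loss; hiding is realistic only for weak signals or for contamination near 25–30%.

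Fourth, the reach is limited. The PSQI outcome is measured in patients and is untouched. The before-and-after comparison is made within patients; healthy values supply its candidate list and direction, not its test.

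What the reply does not answer is that no item in the detailed criteria says how unrecognised sleep disorder is ruled out. The lists go down to ECG and blood lipids, so this is a choice as written rather than detail lost in condensing.

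**Conclusion.** The point holds in a limited form. As written, the plan probably keeps out people with known insomnia, but not those with unrecognised insomnia or another unrecognised sleep disorder. On the text shown, it leaves no means of checking later. The effect on the discovery contrast is bias toward zero and some lost power: from about 89–90% to 81–83% at 10% contamination, and to about 86% at 5%.

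These sizes rest on three assumptions: 10% is an upper bound, affected controls carry the full patient shift, and 0.8 carries over from the PSQI to a metabolite. The gap in the criteria does not depend on them. Because the loss is modest and confined to the metabolomic contrast, this is a should-fix and not a fatal flaw.

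**What to change.** In 2.2.2.2 add for healthy people:
- PSQI below 5 at enrollment. Section 2.8.1.1 supplies the threshold: "A score of ≥5 on the PSQI indicates that clinical treatment may be needed". It does not overlap the patient entry range, which starts above 5.
- Not meeting ICSD-3 criteria for insomnia.
- None of the other sleep disorders listed for patients in 2.2.3.1.

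In 2.8.3 state that the PSQI is given and recorded at the single healthy visit, when serum is drawn. If Figure 2 or the full protocol already provides for this, the text need only be brought into line.

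Section 2.14 says that recruitment is under way, so some controls may already have given serum without a PSQI. Flag them, and report the Group A versus healthy screen with and without them only if enough screened controls remain. Dropping all of them could otherwise leave too few for an informative comparison.

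The cost is a short amendment, one brief questionnaire for 33 people at a visit that already takes place, and a few extra screen failures. The planned sample size does not change.

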#### Exclusion criteria

2.2.3

##### Exclusion criteria for insomnia patients

2.2.3.1

Neuroendocrine, cardiovascular, cerebrovascular, hematopoietic system, tumor and other serious diseases;Sleep disorders caused by depression, anxiety, schizophrenia or other serious mental illnesses with HAMA score >14 and/or HAMD score >17;Other sleep disorder disorders such as obstructive sleep apnea, rapid eye movement (REM) sleep disorder or restless legs syndrome;Those who are not suitable to receive acupuncture treatment, such as those who are pregnant or breastfeeding;Those who have received acupuncture treatment for insomnia in the past month;those with alcohol and/or other drug abuse or dependence.

##### Exclusion criteria for healthy people

2.2.3.2

Pregnant and lactating women;Alcoholics and smokers.

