### Study design

2.1

The study design is a single-center, double-blind, clinical trial to investigate the metabolic pathways and possible mechanisms underlying the efficacy response of electroacupuncture for insomnia. The study protocol follows the SPIRIT guidelines, 99 subjects will be recruited and divided into an insomnia group and a healthy group. The International Classification of Sleep Disorders, Third Edition (ICSD-3) diagnostic criteria will be used to diagnose subjects with insomnia. Those who meet the inclusion criteria will also sign an informed consent form, complete the following scale assessments, and have their serum collected: PSQI and ISI to measure sleep; HAS to measure hyperarousal state; HAMD and HAMA to measure mental state; and FSS to measure physical and mental fatigue, sleep diary to measure sleep behavior, and MoCA to measure cognition to gather baseline assessment data. This will be followed by 4 weeks of treatment. Retesting of the above scales will be completed at the end of treatment and at 3 months follow-up, as well as serum collection’s will be completed at the end of treatment. The healthy group will complete serum collection at enrollment. The insomnia group will be randomly divided into Group A and Group B, matched with the healthy group. Group A and the healthy group will be screened for differential metabolites using metabolomics analysis with non-targeted UPLC-Q/TOF-MS, and Group B will be quantified for the screened differential metabolites using metabolomics with targeted UPLC-QQQ-MS/MS. The flow chart of the experiment is shown in **Figure 1**. The flow schedule is shown in **Figure 2**.

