
There are some limitations of this study. First, the follow-up period of this study was short due to limited conditions. However, because most insomnia patients have a long duration of illness and are difficult to cure, it is necessary to observe the long-term effects of acupuncture on regulating metabolism and improving sleep quality. Secondly, the research employed a single-center design, which may introduce experimental bias and result in a single sample that lacks representativeness. More influencing factors should be considered and the results should be further validated and explored in a large sample population. Finally, the serum collected from subjects in this study was not fasting serum and may be affected by more factors, which may lead to bias and thus affect the results. Therefore, further metabolic studies with multicenter, large samples and extended follow-up periods are needed in the future.

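### Smokers and people with abnormal routine laboratory tests can enter only as insomnia patients, so some metabolites screened as insomnia-related may reflect smoking or milder metabolic abnormality

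*Protocol article*

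**What the plan says.** All references are to the protocol article.

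**Healthy group.** Section 2.2.2.2 requires "Normal blood count, liver function, kidney function, electrocardiogram, blood glucose, and blood lipid after consultation and health examination" and also "healthy, no previous organic or functional diseases or psychiatric disorders". Section 2.2.3.2 excludes "Alcoholics and smokers", along with pregnant and lactating women.

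**Insomnia group.** Besides age, communication and cognitive ability, smartphone use and consent, section 2.2.2.1 asks for "Meet ICSD-3 diagnostic criteria;5 points < PSQI < 17 points;not receiving psychotropic medication". On physical health, section 2.2.3.1 excludes "Neuroendocrine, cardiovascular, cerebrovascular, hematopoietic system, tumor and other serious diseases". On substances, it excludes "those with alcohol and/or other drug abuse or dependence". Neither section mentions smoking or any laboratory value.

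**Data from the healthy group.** Sections 2.1 and 2.8.3 list one serum sample at enrolment. No sleep questionnaire and no PSQI limit is stated for this group.

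**Use of the contrast.** Section 2.1 sets Group A against the healthy group for the untargeted screen; Group B then has the screened metabolites quantified. Section 2.9.3.2.4 selects on VIP>1 from OPLS-DA and a two-sided univariate p<0.05. Section 2.13 names a t-test or rank-sum test, with no covariate. The Discussion says that the metabolites found this way will be taken as associated with insomnia and then followed before and after treatment.

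**The concern.** Two groups that are compared to find markers of a disease should differ in the disease and, as far as possible, in little else. Here the eligibility rules themselves create other differences. A smoker, or a person with mildly raised glucose or lipids or a mildly abnormal liver test, can enter as a patient but never as a control.

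The laboratory criteria also bear on the biology under study. The Introduction names amino-acid and glycolipid metabolism and altered glucose metabolism as features of insomnia, and the Discussion adds triglycerides, cholesterol and free fatty acids. Controls are thus selected on quantities close to those being compared.

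At stake is the meaning of the metabolomic primary outcome: a metabolite could pass the screen and be reported as insomnia-related when it marks smoking or metabolic health. Separately, controls with unrecognised insomnia would blur true differences.

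**Working it through.** **1. Criteria side by side**

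| Factor | Healthy group | Insomnia group |
|---|---|---|
| Smoking | excluded (2.2.3.2) | not mentioned |
| Glucose, lipids, liver, kidney, blood count, ECG | must be normal (2.2.2.2) | not mentioned |
| Previous disease | none, organic, functional or psychiatric (2.2.2.2) | serious disease excluded (2.2.3.1) |
| Alcohol | alcoholics excluded | abuse or dependence excluded |
| Sleep | no scale or limit stated | ICSD-3 and a PSQI range |

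Alcohol is roughly balanced and is not part of the point. Smoking, milder laboratory abnormality and sleep assessment are not balanced.

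**2. Does a later step remove the imbalance?** The stated tests adjust for nothing. Matching cannot balance smoking if patients may smoke and controls may not. A regression term for smoking adds nothing either: with no smoking controls, the adjusted group difference is simply non-smoking patients against controls. Group B comes from the same patient pool, so quantifying the hits there cannot separate insomnia from smoking.

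**3. Illustration of size.** The plan gives no figure on this point to reproduce. It states neither the share of patients who smoke, *p*, nor the shift of a metabolite with smoking, *D* (in SD units). Both are assumed: *p* = 10-40%; *D* = 0.2, 0.5 or 1 SD. With 33 per group, no true insomnia effect and no smoking controls:

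- Spurious difference = *p* × *D*
- Variance in patients = 1 + *p*(1 − *p*)*D*²; in controls = 1
- SE = √[(variance in patients + 1)/33]
- P(p<0.05) ≈ 1 − Φ(1.998 − difference/SE) + Φ(−1.998 − difference/SE), where 1.998 is the two-sided 5% t value on 64 degrees of freedom

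For *p* = 0.3, *D* = 1: difference 0.30; SE = √(2.21/33) = 0.259; ratio 1.16; probability about 0.20. Simulation of the smoker mixture with a t-test gives 0.21.

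Simulated chance of p<0.05 for one metabolite:

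| Smoking shift | 10% smoke | 20% | 30% | 40% | Spurious difference |
|---|---|---|---|---|---|
| 0.2 SD | 5% | 5% | 6% | 6% | 0.02-0.08 SD |
| 0.5 SD | 5.5% | 7% | 9% | 12% | 0.05-0.20 SD |
| 1 SD | 7% | 12% | 21% | 33% | 0.10-0.40 SD |

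The nominal rate is 5%. Section 2.5 speaks of 33 patients being split 1:1; if Group A has 16 rather than 33, the 1 SD row runs from about 7% to 25%. These are univariate figures; the VIP>1 condition is not modelled.

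**The case against.** **What stands.** Serious neuroendocrine, cardiovascular and other disease is excluded among patients, so the laboratory gap concerns milder abnormality only. The substance exclusion might be stretched to nicotine dependence, but smoking is not named. For a metabolite that responds weakly to smoking the distortion is negligible, as the 0.2 SD row shows. The PSQI outcome is untouched.

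**Stronger readings that a reader might infer, and why the documents do not support them.**

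- *That sleep in controls is never measured, or that about 3 of 33 have insomnia.* The text lists only serum, but the assessment schedule (Figure 2) is not shown, and the wording in 2.8.3 may limit timing rather than content. Applying the Introduction's 10% population prevalence ignores the consultation, health examination and disease-history screen. That screen may still miss unrecognised insomnia, which the Introduction says is underdiagnosed; no count follows from this.
- *That such contamination costs a calculable amount of power.* The effect size of 0.8 in section 2.3 is for the PSQI. The protocol makes no power claim for the metabolite contrast.
- *That every later result is contaminated.* The Introduction also describes a comparison of patients before and after treatment. Stable traits such as smoking largely cancel there, although the choice of metabolites carried over from the case-control screen remains affected.
- *That patients should be required to have normal laboratory values.* The protocol holds that insomnia itself disturbs glucose and lipids, so this could remove part of the phenotype under study.
- *That unnamed matching factors, non-fasting serum and draw time add to the fault.* Section 2.1 says "The insomnia group will be randomly divided into Group A and Group B, matched with the healthy group"; an article may leave the factors and the sampling clock to the full protocol. Non-fasting serum is already declared ("the serum collected from subjects in this study was not fasting serum and may be affected by more factors"), applies to all participants and is not an eligibility imbalance.

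**Conclusion.** The point holds in limited form. The unequal smoking and laboratory criteria are explicit, and the planned case-control screen does nothing to offset them. Some metabolites reported as insomnia-related may therefore mark smoking or milder metabolic abnormality, and the stated limitations do not mention this. How many cannot be known from the documents: under assumed smoking shares and shifts, the chance of a false signal for one smoking-sensitive metabolite runs from barely above 5% to about one in three. The absence of a stated sleep scale or PSQI ceiling for controls is a secondary weakness of unquantified size. The change should be made while recruitment is open (section 2.14).

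**What to change.** 1. **Smoking.** Apply the smoking exclusion to both groups from now on. Record smoking status for all insomnia patients already enrolled and repeat the Group A versus healthy screen in non-smokers.
2. **Laboratory tests.** Record the same tests in patients where available. Report the screen restricted to patients with normal results as a sensitivity analysis, not as an entry criterion.
3. **Sleep in controls.** Give healthy participants the PSQI and ISI at enrolment and require a PSQI of 5 or less, which does not overlap the patients' entry range of more than 5. Section 2.8.1.1 treats a score of exactly 5 as possibly needing care, so the sponsor may prefer a ceiling below 5.

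**Cost.** A protocol amendment, slightly slower recruitment, two short questionnaires for 33 people, and less precision in the restricted analyses. If 10-40% of 33 Group A patients smoke (assumed), about 30 to 20 remain (33 × 0.9 = 29.7; 33 × 0.6 = 19.8).
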